### Focus groups

Qualitative data will be collected only from the EG, at baseline and end of PR. Each focus group will last approximately 90 min and will be audio-recorded and transcribed verbatim, with field notes taken to capture participants’ nonverbal expressions. Participant’s identifying information will not be recorded on the transcripts. We will attribute fictitious names to each participant to ensure anonymity. Interview guides using open-ended questions were developed to explore: a) pre-intervention – knowledge, perceptions, experiences and perceived needs of palliative care (e.g., “What words do you associate with palliative care?”; “Can you remember the first time that you heard about palliative care?”, in affirmative cases: “Please, share your experience. When was it? What did it mean to you?”); and general opinion on integrating palliative care education in PR; and b) post-intervention – acceptability, perceived benefits, added value and impact of integrating palliative care education in PR (e.g., “When do you think is the most appropriate time for assessment by a specialist palliative care team?” and “Did the integration of palliative care education in the PR program had any impact on your physical, psychosocial and spiritual well-being?”); and suggestions for its improvement. The researcher moderating the focus groups will be responsible to get all participants to talk and fully explain their answers, remaining neutral and listening attentively with sensitivity and empathy.

### Sample size calculation

The sample size was estimated for the primary outcome measure, PaCKS, in G*Power 3.1.9.4, for the time*group interaction of a mixed analysis of variance (ANOVA) with two groups (control and experimental) and two timepoints (at baseline and end of PR). We considered an α of 0.05, a power of 0.80, a correlation among repeated measures of 0.5, a nonsphericity correction of 1 and an expected effect size f of 0.25 [76]. The calculated sample size was 34 and considering a possible 40% dropout and missing data rate [77], the final sample size was determined to be 58 (29 in each group).

### Statistical analysis plan

A mixed-methods approach [78] will be used to explore the effects of the intervention. First, quantitative and qualitative data will be analyzed separately, in a parallel process.

Quantitative data will be processed using IBM SPSS Statistics version 29.0 and RStudio 2022.12.0. Categorical variables will be presented as counts(percentages). Quantitative variables will be summarized using mean ± standard deviation or median[interquartile range], based on the normality of data distribution which will be explored with Shapiro–Wilk test. The EG will be compared with the CG for the primary outcome with a mixed ANOVA if assumptions are met, followed by a multiple pairwise comparison with Bonferroni correction; otherwise, an aligned rank transform-ANOVA will be performed instead. Imputation methods will be used to deal with missing data as appropriate, followed by sensitivity analyses. For all statistical analyses, a *p* value < 0.05 will be considered statistically significant.

Qualitative data will be processed using Web Qualitative Data Analysis (WebQDA) for inductive thematic analysis [79]. The proposed six-step procedure will be followed: 1. familiarizing with the data; 2. generating initial codes; 3. searching for themes; 4. reviewing themes; 5. defining and naming themes; and 6. producing the report [79]. Trustworthiness of the qualitative research will be ensured using the credibility, transferability, dependability, and confirmability criteria [80]. Credibility will be ensured by a) researcher triangulation i.e., each focus group will be transcribed and preliminary coded by one researcher ([name]); then, data will be independently analyzed by two researchers ([name] and AM), which will agree on themes and subthemes; and finally, all the research team ([name], AM and DJ) will review the themes and subthemes until consensus is reached; and, b) engagement with data by all the research team. Transferability will be ensured by a comprehensive and detailed description of the research setting and participants. Dependability will be ensured by having an independent researcher that will examine, explore and challenge the processes of data collection, analysis and interpretation. Confirmability will be ensured by researcher reflexivity, peer debriefing and member checking among people with COPD or ILD and their family and/or friend caregivers.

Afterwards, we will compare quantitative and qualitative data and merge them through joint displays for integration of both methods in the final interpretation of the results.

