### Outcomes

The primary outcome will be knowledge about palliative care evaluated with the Palliative Care Knowledge Scale (PaCKS) [45]. Data will be collected at baseline (T0) and end of PR (T1). At 6-months post-PR (T2), only patient-reported outcome measures will be collected. Table 2 provides a detailed description of primary and secondary outcomes that will be assessed throughout the study period. Some outcomes, such as functional capacity, peripheral muscle strength and balance are not expected to be influenced by education, however they are important to assess the effectiveness of PR delivery.

**Table 2 Tab2:** Overview of outcomes and outcome measures evaluated in people with chronic obstructive pulmonary disease or interstitial lung diseases and their family and/or friend caregivers

Outcome	Outcome measure	Description	MCID^a^	People with COPD or ILD	Family and/or friend caregivers	T0	T1	T2
Knowledge about palliative care	PaCKS [45]	- Self-reported questionnaire with 13 items which are true or false. A broad range of topics are assessed, including goals, target population and timing of palliative care, as well as symptoms and problems that palliative care addresses - For each statement, “True”, “False” and “I don’t know” options are provided, and a mark is given for each correct answer - Scores range from 0/13 to 13/13, with higher scores indicating higher knowledge	Not applicable	⬤	⬤	×	×	×
Attitude towards palliative care referral	“Would you like (your loved one) to be referred to a specialist palliative care team at this time?” [46]	- “Would you like to be referred to a specialist palliative care team at this time?” and “Would you like your loved one to be referred to a specialist palliative care team at this time?” will be asked to people with COPD or ILD and their family and/or friend caregivers, respectively - Possible answers are “Yes”, “No” or “Don’t know”	Not applicable	⬤	⬤	×	×	×

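### The data-dependent switch of the primary test to an aligned-rank-transform ANOVA gains no validity over the planned mixed ANOVA and can, under some score distributions, raise the false-positive rate

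*Protocol article*

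**What the plan says.** The Statistical analysis plan section of the protocol article fixes a two-step rule for the primary outcome: "The EG will be compared with the CG for the primary outcome with a mixed ANOVA if assumptions are met", and "otherwise, an aligned rank transform-ANOVA will be performed instead". Shapiro-Wilk is the only check named there, and it is named for choosing between mean and median summaries, "based on the normality of data distribution which will be explored with Shapiro–Wilk test". The section does not say which check decides between the two primary tests. For all analyses, a p "value < 0.05 will be considered statistically significant".

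The Sample size calculation section sizes the trial, at the 5% level, for the time-by-group interaction of the mixed ANOVA only: "a power of 0.80, a correlation among repeated measures of 0.5, a nonsphericity correction of 1 and an expected effect size f of 0.25".

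Table 2 in the Outcomes section describes PaCKS as 13 items with a don't-know option and one mark per correct answer: "Scores range from 0/13 to 13/13, with higher scores indicating higher knowledge". The article gives no expected mean, SD, distribution or share of zeros.

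**The concern.** A fallback test is worth having if the main test loses its level when its assumptions fail and the fallback does not. Here the order may be reversed. PaCKS takes only 14 values, and a don't-know answer earns nothing, so ties at zero are possible. Ties and skew are what a normality check would flag.

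ART subtracts the group and time means from every score before ranking. Scores that were tied at zero then take four different values, one for each arm and time, and ranking can turn tiny chance differences between the sample means into large rank gaps. If so, the stated 5% level would be least secure in the data for which the fallback is meant.

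Two further points need no assumption about zeros. The test reported may not be the one for which the sample size was calculated. And an ART p-value does not by itself give a difference in PaCKS points.

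**Working it through.** **1. Reproducing the plan's sample size.** Inputs from the Sample size calculation section: f = 0.25, correlation 0.5, two timepoints, nonsphericity correction 1, alpha 0.05, two groups.

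- Noncentrality: λ = f² × N × m × ε / (1 − ρ). For N = 34, λ = 0.0625 × 34 × 2 × 1 / 0.5 = 8.5. With 1 and 32 degrees of freedom the power is 0.807.
- For N = 32, λ = 8.0 and the power is 0.781. So 34 (17 per arm) reproduces.
- 34 / (1 − 0.40) = 56.7, rounded up to 57, or 58 for equal arms (29 each). This also reproduces.

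The calculation covers the raw-score interaction test, not ART.

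**2. How alignment breaks ties.** For the interaction, the aligned value is Y − (group mean) − (time mean) + (grand mean). At either time, the zeros of the two arms now differ by the difference between the overall arm means, which is pure chance under the null. Suppose a share z of n people per arm score zero and no other aligned value falls between the two clusters. The clusters' average ranks then differ by n × z, which shifts the arm's mean rank by n × z².

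The interaction depends on the change in this shift, n × (z₀² − z₁²), where z₀ and z₁ are the shares at baseline and end of PR. With equal shares it largely cancels. With 29 per arm and zeros falling from 60% to 30%, it is 29 × (0.36 − 0.09) = 7.8 ranks. This shows why a fall in zeros matters but does not predict the size: a fall from 50% to 10% gives 29 × (0.25 − 0.01) = 7.0 ranks, yet ART simulates at only 5.7-7.8% there (29 per arm, zero-inflated binomial).

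**3. Simulation under no effect.** Both arms were drawn from the same distributions, with 17 or 29 per arm and scores from 0 to 13 (zero-inflated binomial, zero-inflated beta-binomial, or skewed beta-binomial). Latent correlation over time was 0.3, 0.5 or 0.8, with 10,000 to 20,000 trials per setting. The interaction F test of a 2 × 2 mixed ANOVA is equivalent to a t test on change scores; for ART the same test is applied to the aligned ranks. All zero shares are assumptions. The ranges span arm sizes, distributions and correlations.

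| Zeros, same in both arms | ART rejection rate at nominal 5% |
|---|---|
| 0-20% at baseline | 4.7-6.5% |
| 30% at baseline | 5.0-6.7% |
| 40% at baseline | 5.4-7.8% |
| 40-80%, no change over time | 5.5-8.0% |
| 60%, fall of 10 points or less | 6.4-8.2% |
| 50% falling to 25% | 5.8-11.0% |
| 60% falling to 30% | 7.0-18.6% |
| 70% falling to 40% | 9.6-24.3% |
| Skewed, no added zeros: 61-63% falling to 39-43% | 9.9-15.7% |

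The raw-score mixed ANOVA stayed at about 4.3-5.7% throughout. Baseline-adjusted ANCOVA, in a separate set of simulations with baseline zeros up to 60%, stayed at 4.7-5.5%, and with HC3 standard errors at 3.9-4.8%.

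**4. If the trigger were Shapiro-Wilk in any cell at 0.05** (an inferred rule; 3,000 trials per setting, 29 per arm). The switch occurs in essentially every trial with 40% or more baseline zeros. The overall rate is then 6.5% (40% falling to 20%), 10.1% (50% to 25%) and 13.9% (60% to 30%). With no added zeros the switch still occurs in 57% of trials, but the rate is 4.9%.

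**The case against.** The strongest reply is that the risky pattern is assumed. The Background speaks of inadequate knowledge and misperceptions, not of people scoring nothing. A zero needs all 13 items wrong or unknown, and someone who guesses true or false from a misperception will usually score some marks. Doubling also needs a large fall in zeros in the control arm, whose education topics include no palliative care session. All of this stands. Retesting on the same 13 items, the referral questions put to both arms and possible referral in either arm could lift control scores, but nothing in the article supports a particular fall.

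The rule is also written down in advance, and the analyst is to be blinded. That answers a charge of picking the favourable result. It does not give the fallback any advantage.

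A reader might infer three stronger things that the article does not support:

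- **That this trial's false-positive rate will double.** Fourteen values alone cause no inflation, and many zeros without change over time give at most about 8%.
- **That the switch is almost certain.** This rests on a Shapiro-Wilk gate for the primary test, which the article does not state. How assumptions are checked may properly sit in a fuller plan.
- **That no difference in points would be reported.** The article plans mean or median summaries and does not rule such an estimate out.

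**Conclusion.** The concern holds in conditional form. The article states a rule under which the primary test may depend on the outcome data and may differ from the test that was sized. Over the settings examined the raw-score interaction test needs no rescue, so the switch gains no type I error protection and can lose some.

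The likely cost is small if zeros are at or below about 40%: roughly 5-6% in most settings, with 7.8% the highest seen. It is moderate, about 6-8%, with 50-60% zeros and little change. It reaches about 10% or more only with around half or more at zero at baseline and a marked fall, about 20 points or more, common to both arms.

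These sizes rest on assumed zero shares, identical score distributions in the two arms under the null, and 17 to 29 people per arm. Because the article gives no PaCKS distribution, where this trial falls in that range cannot be said.

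**What to change.** Replace the conditional sentence with one named primary analysis that applies whatever a normality check shows. The preferred choice is ANCOVA of end-of-PR PaCKS on group, adjusted for the baseline PaCKS already being collected. At the planning correlation of 0.5 and equal SDs at both times, its residual variance is (1 − 0.5²) = 0.75 of σ², against 2 × (1 − 0.5) = 1.00 of σ² for change scores, so the planned sample size is not weakened. The minimum alternative is to keep the mixed-ANOVA time-by-group interaction, unconditionally; it is the test that was sized and it needs no other change.

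In either case, state that the between-group difference will be reported in PaCKS points with a 95% CI. Keep the ART-ANOVA, or a permutation or HC3 version, only as a labelled sensitivity analysis.

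The cost is about one sentence and the loss of a rank-based primary p-value. ANCOVA also departs from the time-by-group test named in the abstract, which would need the matching edit. HC3, if used, is slightly conservative at this size.

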PR could be an ideal setting to identify and assess unmet needs of people with COPD or ILD and their family and/or friend caregivers and introduce palliative care [3, 19, 27]. Education and psychosocial support sessions are a well-established component of PR. Including palliative care educational content (e.g., concept, role and goals of palliative care, symptom control, disease impact, psychosocial support and planning for the future) in these sessions and actively involving family and/or friend caregivers represents an important opportunity to introduce palliative care in PR. Indeed, already a decade ago advance care planning was mentioned as one of the educational topics in PR [28], which has been well received by patients [29]. Moreover, across the PR program, individuals could be timely referred to a specialist palliative care team, which has the potential to add particular benefit in breathlessness management, advance care planning and psychosocial support. Another possible strategy to improve patients’ and family and/or friend caregivers’ care is educating and training rehabilitation staff in palliative care issues and advanced communication skills [3, 7, 22, 27]. In fact, placing focus on palliative care in PR has the potential to provide the best chance of timely addressing unmet needs of those with COPD or ILD and their family and/or friend caregivers. However, the direct effects of this integrated care model on patients’ and family and/or friend caregivers’ outcomes have not been studied before.

We hypothesize that by integrating palliative care education in PR for people with COPD or ILD and their family and/or friend caregivers we will improve knowledge about palliative care. Furthermore, we hypothesize that by enhancing educational opportunities, namely including the topic of palliative care in PR we will change the attitude towards palliative care referral, improve symptoms, disease impact, HRQoL, needs, knowledge about the disease and reduce burden of providing care.

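### A blanket p < 0.05 significance rule covers about 21 hypothesised secondary measures, with no correction, ordering or exploratory label

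*Protocol article*

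**What the plan says.** The Statistical analysis plan section sets one threshold for everything: "For all statistical analyses, a *p* value < 0.05 will be considered statistically significant". It names a between-group test (mixed ANOVA, or an aligned rank transform ANOVA if assumptions fail) only for the primary outcome, PaCKS. That test is "followed by a multiple pairwise comparison with Bonferroni correction", which is the only multiplicity adjustment in the article. No key secondary outcome, testing order or split of alpha is given.

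The Background adds a second hypothesis to the primary one, namely that through the enlarged education programme "we will change the attitude towards palliative care referral, improve symptoms, disease impact, HRQoL, needs, knowledge about the disease and reduce burden of providing care". That is seven domains. Six carry a direction (improve or reduce); attitude to referral is only expected to change.

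Table 2 schedules the measures for all seven domains at baseline, T1 and T2, in patients, caregivers or both. The aims paragraph of the Background uses the verb explore for the primary aim and for the secondary aim on effects alike.

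**The concern.** The fault lies in a rule that the article writes down, not in a detail left out of it. A hypothesis of benefit in several domains, joined to a rule that any p value below 0.05 is significant, lets one low p value among many be reported as a significant effect and read as support for the second hypothesis.

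The trial is small (58 randomised, 34 expected to be evaluable) and is powered for PaCKS alone. The hypothesised secondary measures are self-reported by participants who know their allocation. An isolated significant result on quality of life, symptoms or caregiver burden would be weak evidence, yet the rule would give it the same label as the primary test.

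**Working it through.** **The plan's own figure.** The Sample size calculation section uses "We considered an α of 0.05, a power of 0.80, a correlation among repeated measures of 0.5" and "an expected effect size f of 0.25", for "two groups (control and experimental) and two timepoints (at baseline and end of PR"). For the G*Power within-between interaction, the noncentrality is N × f² × m / (1 − ρ), with m = 2 timepoints, ρ = 0.5 and degrees of freedom 1 and N − 2.
- N = 34: 34 × 0.0625 × 2 / 0.5 = 8.5, power 0.807.
- N = 32: 32 × 0.0625 × 2 / 0.5 = 8.0, power 0.781.

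So 34 reproduces. Then 34 / 0.60 = 56.7, which rounds up to 57 and to 58 for equal arms. The sample size is not in dispute. It matters here because it is set for PaCKS only.

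**Counting the hypothesised measures (Table 2, total scores only).**
- Patients, 12: two attitude questions, pain, mMRC, FACIT-FS, LCQ, HADS-A, HADS-D, CAT, SGRQ, SNAP, BCKD.
- Caregivers, 9: two attitude questions, pain, FACIT-FS, HADS-A, HADS-D, CSNAT, BCKD, ZBI.
- Together 21 at T1, or 42 if each is tested again at T2.

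Left out because no benefit hypothesis names them: functional performance, functional capacity, muscle strength, balance, adherence, adverse events and referral.

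**Chance of at least one false significant result when no measure is affected.** Each test is taken as two-sided at 0.05 (the article does not state sidedness), so the critical value is z = 1.96. "Benefit" means z > 1.96 in favour of the experimental arm, at 0.025 per test. For attitude, where no direction is hypothesised, one direction has to be chosen.

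For k independent tests the chance is 1 − 0.95^k in either direction and 1 − 0.975^k in the benefit direction:
- k = 7 (one test per domain): 0.30 and 0.16
- k = 21: 0.66 and 0.41
- k = 42: 0.88 and 0.66

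For correlated tests, take equicorrelated standard normal statistics with common correlation ρ and average over the shared component c:
- either direction: 1 − E{[Φ((1.96 − √ρ·c)/√(1−ρ)) − Φ((−1.96 − √ρ·c)/√(1−ρ))]^k}
- benefit only: 1 − E{[Φ((1.96 − √ρ·c)/√(1−ρ))]^k}

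| Tests | Direction | ρ = 0 | ρ = 0.3 | ρ = 0.5 | ρ = 0.8 |
|---|---|---|---|---|---|
| 12 (patients, T1) | either | 0.46 | 0.40 | 0.32 | 0.19 |
| 12 (patients, T1) | benefit | 0.26 | 0.20 | 0.16 | 0.09 |
| 21 (all, T1) | either | 0.66 | 0.56 | 0.43 | 0.23 |
| 21 (all, T1) | benefit | 0.41 | 0.29 | 0.22 | 0.11 |
| 42 (all, T1 and T2) | either | 0.88 | 0.76 | 0.58 | 0.28 |
| 42 (all, T1 and T2) | benefit | 0.66 | 0.41 | 0.29 | 0.14 |

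For the 21 tests at ρ = 0.5 the ratio to a single test is 0.43 / 0.05 = 8.6 in either direction, and 0.216 / 0.025 = 8.6 in the benefit direction.

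**The case against.** **No secondary test is described.** The article names a test only for PaCKS. Table 2 shows what is measured, not what is tested, and a full analysis plan may set out the rest. This stands as a limit on the point: the test counts are inferred, and the lack of a hierarchy in a condensed article would not be a finding by itself. It does not remove the point, because the sentence on significance extends expressly to all analyses and so governs any secondary test that is run.

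**The trial calls itself exploratory.** The aims, the analysis section and the Discussion all speak of exploring effects, and the Clinical implications section expects preliminary evidence. With one powered primary outcome, unadjusted secondary tests are common practice. That is fair, and it keeps the severity modest. But the same verb describes the primary aim, which is powered and formally tested, so it does not mark the secondary outcomes as a separate, non-confirmatory class. The Abstract, moreover, says the study aims to demonstrate impact.

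**The upper figures are too high.** This stands in part. Independence is implausible for the same instrument in the same person at T1 and T2. The second attitude question goes only to those who did not say yes to the first, so those two are linked. The values at ρ = 0 are therefore outer limits, above all the 0.88 for 42 tests.

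**A stronger reading is tempting.** A reader might infer that every secondary outcome is tested in support of a directional hypothesis, and that a false finding of benefit is therefore likely. The documents do not support this. The Outcomes section says functional capacity, strength and balance should not respond to education. Functional performance, adherence, adverse events and referral appear in no hypothesis, and attitude is only expected to change. In the benefit direction at ρ = 0.5, the chance is 0.22 for 21 tests and 0.29 for 42. Among the cases tabulated it passes one half only for 42 independent tests.

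**Conclusion.** The point holds in a limited form. The article pairs hypotheses of benefit or change in seven secondary domains with an uncorrected significance label for all analyses, and nothing in it separates those outcomes from the primary test. If the 21 hypothesised measures are each tested once at T1 and none is affected, the chance of at least one false significant result is about 0.43 in either direction (range 0.23 to 0.66). It is about 0.22 in the benefit direction (range 0.11 to 0.41). A single test gives 0.05 and 0.025.

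These figures rest on my count of total scores from Table 2, two-sided testing, a common correlation of 0.5 (range 0.8 to 0) and a null effect on every measure. The article gives neither a list of tests nor a correlation between outcomes. The inflation is well above the single-test level in every case tried, so the conclusion does not depend on the exact count. It is a cheap improvement of modest severity and does not affect the primary analysis.

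**What to change.** 1. In the Statistical analysis plan section, limit the p < 0.05 significance rule to the primary PaCKS time*group test.
2. In the same section, state that all secondary outcomes, in patients and caregivers and at T1 and T2, are exploratory and will be reported as between-arm estimates with 95% confidence intervals and no claim of significance.
3. In the Background, reword the second hypothesis so that it states an exploratory aim.

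This takes about three sentences and no new data. By the article's timeline data collection ends in June 2026, so the change can be made before the final analysis. The downside is that the sponsor gives up calling isolated secondary p values below 0.05 significant. An ordered or Holm-adjusted list would be an alternative, but the documents offer no basis for choosing its order or content, so I do not recommend one here.
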